### Participants

2.2

#### Inclusion criteria

2.2.1

Infants who meet all of the following criteria will be included**:** (1) very preterm infants with a GA of less than 32 weeks; (2) presence of respiratory distress after birth, such as a respiratory rate of more than 60 breaths/min, grunting, nasal flaring, intercostal retractions, and/or cyanosis; (3) born in the authors’ hospital.

#### Exclusion criteria

2.2.2

Infants who meet any of the following criteria will be excluded: (1) infants who have received PS treatment in the delivery room or external setting after birth; (2) infants with known or confirmed congenital abnormalities, especially cardiopulmonary deformities during diagnosis or treatment; (3) presence of severe complications at birth (severe asphyxia, hemorrhagic shock, pneumonia, pneumothorax, early-onset sepsis, and pleural effusion) or other diseases not caused by PS deficiency; (4) infants who die within 72 h after birth, are transferred to another hospital for surgery, or have incomplete data; and (5) those with families who do not consent to participate in this study.

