#### Ultrasound group

2.7.1

Lung ultrasonography will be performed within 1 h of admission, followed by lung ultrasound scoring (refer to Figure 2 for the segmentation and scoring methods). In the case of different score patterns in the same area, the worst will be selected. If the lung ultrasound confirms RDS and LUS is more than 8, a full dose of PS will be promptly administered at 200 mg/kg (Poractant Alfa, Curosurf®). If the lung ultrasound does not indicate RDS or if LUS is 8 or less, clinical monitoring will continue. Should the clinical criteria for NRDS be met, a full dose of PS will be administered at 200 mg/kg (Poractant Alfa, Curosurf®). In terms of the administration method, less-invasive surfactant administration (LISA) will be employed for infants in a non-invasive ventilation state, while those in an invasive ventilation state will receive PS via endotracheal tube. Lung ultrasound and scoring will be repeated 4–10 h post the first PS dose administration (with scoring results withheld from the clinical team). Repeated PS administration will occur if the criteria are met, with lung ultrasound scoring conducted prior to each administration (with scoring results withheld from the clinical team). Repeated PS administration will be completed via endotracheal tube.

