Based on prior research, this study protocol has been refined and improved in the following aspects: (1) Patient selection: very preterm infants with a GA of less than 32 weeks will be selected. According to previous study reports, the incidence of NRDS increases gradually with a decrease in GA. The incidence of NRDS in extremely preterm infants (GA ≤28 w) has been reported to be 93%; however, even among late preterm infants at 34 weeks GA, 10.5% of patients were diagnosed with NRDS (29, 30). In preterm infants below 32 weeks GA, early postnatal respiratory distress can be caused by a variety of causes. Differential diagnosis through traditional imaging is not only less sensitive but also brings about the challenges of radiation exposure. Patients often have delayed application or overuse of PS owing to misdiagnosis. Our study will include this population as the research object, hoping to identify NRDS more accurately and guide PS application through non-invasive methods in the early stage. (2) The clinical application of LUS was optimized: most previous studies judge whether to use PS only according to LUS, ignoring the possibility that other diseases causing respiratory distress may be misdiagnosed as NRDS. The severity of lung lesions caused by different diseases cannot be compared in parallel by LUS. In our study, the researchers first diagnosed NRDS through lung ultrasound and then assessed the severity of NRDS according to LUS and guided the application of PS. The combination of qualitative diagnosis and semi-quantitative assessment was more reasonable. In the diagnosis of NRDS by pulmonary ultrasound, the lesions may appear in any lung field; the pulmonary ultrasound guidelines clearly indicate that the lung lesions of NRDS mainly appear posteriorly, and therefore, the examination of the posterior region should not be ignored (19). In previous studies, in order to avoid moving patients, only the anterior and lateral lung fields were examined and scored, which may affect the accuracy of results (25, 31). In our study, according to the pulmonary ultrasound guidelines for lung partitioning, the anterior, lateral and posterior lungs were comprehensively evaluated and the scores of each lung field were recorded; the final total score was then calculated, which will be more accurate than the calculations in previous studies. (3) Timing of lung ultrasonography: previous studies have limited time points for lung ultrasound assessments, usually within the first 24 h post-birth. However, in the early postnatal period, premature infants experience rapid changes in their conditions and may require repeated administration of PS. Therefore, in our study design, the ultrasound group will undergo multiple lung ultrasound examinations within the first hour after birth, 4–10 h after the initial PS administration, prior to subsequent PS administration, and at 24- and 72-h post-birth. This will be the highest frequency of lung ultrasound examinations among known studies of the same type, and this approach allows for better monitoring of early postnatal lung ultrasound dynamics. Additionally, follow-up lung ultrasonography will be conducted at 1, 2, and 4 weeks after birth, as well as before discharge, thereby providing a basis for prognostic assessment; (4) Treatment method: following the 2022 European Consensus Guidelines on the Management of Respiratory Distress Syndrome, NCPAP combined with LISA was identified as the preferred treatment for preterm infants with spontaneous breathing after birth (2). Therefore, in this study, for infants receiving non-invasive ventilation (NCPAP or NIPPV) and exhibiting spontaneous breathing, priority will be given to the LISA method to reduce the risk of airway injury. This study aims to combine non-invasive diagnosis methods with non-invasive treatment to reduce the requirement for early invasive operations after the birth of preterm infants.

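### Exclusion criterion 3 removes infants by cause of distress, with no time point or diagnostic basis, which conflicts with the mixed-cause target population and allows arm-dependent removal after randomisation

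*Protocol article*

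**What the plan says.** Entry (section 2.2.1) rests on gestational age under 32 weeks, birth in the hospital, and "presence of respiratory distress after birth, such as a respiratory rate of more than 60 breaths/min" or similar signs. No diagnosis of NRDS is needed.

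The Discussion gives the reason for choosing this group: "In preterm infants below 32 weeks GA, early postnatal respiratory distress can be caused by a variety of causes". It continues: "Our study will include this population as the research object, hoping to identify NRDS more accurately". It faults most previous studies for "ignoring the possibility that other diseases causing respiratory distress may be misdiagnosed as NRDS".

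Both arms provide for infants without NRDS. In the ultrasound group (section 2.7.1), "If the lung ultrasound does not indicate RDS or if LUS is 8 or less, clinical monitoring will continue". In the control group (section 2.7.2), surfactant is withheld when the clinical picture does not meet the diagnosis.

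Exclusion criterion 3 (section 2.2.2) lists severe complications at birth, among them pneumonia and pleural effusion, and then adds "or other diseases not caused by PS deficiency". It gives no time point, severity limit or diagnostic method for that addition.

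**The concern.** One part of the protocol studies distress of any cause so that NRDS can be told apart from its mimics. Another part excludes infants whose disease is not surfactant deficiency. Site staff cannot follow both as written, and who is enrolled and analysed depends on which text they follow.

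Two things are at stake. The first is the question answered: the Background motivates the trial partly by misdiagnosis and overuse of surfactant, and the infants who carry that information are those with a cause other than surfactant deficiency. The second is validity: if cause is judged after allocation, the exclusion rests on information that the randomised strategy itself helps to produce.

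**Working it through.** **1. The passages side by side**

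| Place in the protocol | Infant with distress not due to surfactant deficiency |
|---|---|
| 2.2.1 Inclusion criteria | Eligible: symptoms suffice |
| 3 Discussion, patient selection | Part of the named study population |
| 2.7.1 and 2.7.2 | Has a pathway in each arm |
| 2.2.2 Exclusion criteria, item 3 | Excluded |

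**2. When can the clause be applied?** Sections 2.3 and 2.7 randomise on arrival in the NICU, and section 2.7.1 places the ultrasound group's scan within 1 h of admission. The cause will often be unsettled at allocation. The exclusion list also contains items that can be known only later: malformations confirmed during diagnosis or treatment (item 2), and death within 72 h or incomplete data (item 4). Nothing in the text keeps item 3 from being applied late too.

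**3. Why late application can differ by arm.** In the ultrasound group the first scan decides whether RDS is diagnosed and whether surfactant is given at once. In the control group the decision is stated to rest solely on clinical signs and chest x-ray (Abstract). Section 2.1 has every enrolled infant scanned early, but the scan is meant to steer care in one arm only. A label of non-surfactant disease can therefore be reached more readily in that arm.

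**4. The plan's own sample size, reproduced.** Inputs from section 2.12: means 96 h and 86 h, SD 12 h, α 0.05 (two-sided assumed), power 80%, 1:1 allocation.

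- Standardised difference: (96 − 86)/12 = 0.833.
- Two-sample t-test: 23.6, so 24 per arm and 48 in total. Power at 24 per arm is 80.7%.
- Inflation: 48/0.80 = 60. Power at 30 per arm is 88.8%.

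The stated figures reproduce. The contradiction does not alter this arithmetic.

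**5. Illustration if infants are removed after randomisation.** The share is not in the documents, so it is assumed. No other loss and equal removal by arm are also assumed. Number per arm = 30 × (1 − share).

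| Share removed | Left per arm | Power | Randomised to keep 48: 48/(1 − share) |
|---|---|---|---|
| 0% | 30 | 88.8% | 48 |
| 10% | 27 | 85.2% | 54 |
| 20% | 24 | 80.7% | 60 |
| 30% | 21 | 75.0% | 69 |
| 40% | 18 | 68.0% | 80 |

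At 20%, this clause alone uses up the whole inflation. If exclusion happens before randomisation, 60 are still randomised and the table does not apply.

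**6. Cost of keeping them.** Assume that 20% have another cause, gain nothing, and the SD stays at 12. The average difference is 0.8 × 10 = 8 h, the standardised difference is 8/12 = 0.667, and power with 30 per arm is about 72%.

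**The case against.** The strongest defence is that criterion 3 means severe conditions evident at birth and that unrecognised mimics still enter, because randomisation precedes the scan. The pathways in both arms for infants without NRDS support this reading. Its logical part stands: excluding a recognised non-surfactant disease is not the same as requiring proven surfactant deficiency. A reader might infer that the trial enrols only infants already judged surfactant-deficient, or that its hypothesis cannot be tested. The documents do not support either. Infants with undifferentiated distress remain eligible, the ultrasound pathway also serves milder disease with a score of 8 or less, and infants whose NRDS would be recognised late on clinical signs remain. Earlier treatment and ventilation duration can still be compared.

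The defence does not settle the text, however. The clause about other diseases reads as a separate alternative to complications at birth, and if the narrow meaning is intended, the wording has to say so.

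A reader might also try to size the problem from the NRDS incidences in the Discussion (93% at 28 weeks or less, 10.5% at 34 weeks). That fails: they are not stated to be incidences among infants with distress, and nothing is given for the weeks between.

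Finally, removal is not the only route to lower power. Under the assumption in step 6 of the working, keeping 20% non-responders gives about 72%, against about 81% after removing them. That is a fair point about cost, but not a reason to remove infants after allocation.

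**Conclusion.** The point holds as a contradiction in the eligibility text. The clause conflicts with symptom-based entry, with the stated study population and with the pathways in both arms. Because it has no time point or diagnostic basis, it can be applied after randomisation, where it would take out infants in whom ultrasound could rule NRDS out and could do so unequally by arm. This weakens the rule-out and overuse part of the rationale and can bias the comparison of ventilation duration; the timing part stays testable.

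The size is unknown. Power of 85% to 68% for 10% to 40% removed is an illustration. It rests on an assumed share, the plan's effect and SD, a two-sided test, no other loss, and removal after randomisation without replacement. The possible bias from unequal removal cannot be quantified from the documents. The contradiction itself depends on none of these figures. It should be corrected.

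**What to change.** - In criterion 3, delete the open clause about other diseases, or limit the whole criterion to conditions diagnosed before randomisation by means that are the same in both arms.
- State that an infant whose distress is later attributed to a cause other than surfactant deficiency stays in the trial and in the analysis of the randomised arm.
- Reconcile the named exclusions with the rest of the text. Pneumonia is excluded by name, yet the Background lists it as a mimic, so deleting the open clause alone would not fully match eligibility to the Discussion. Pleural effusion is an exclusion in section 2.2.2 but one of the ultrasound features of RDS in section 2.8.

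This is a short amendment with no new procedures. The downside is a more mixed group, which may dilute the effect: to about 72% power at 30 per arm in the 20% example. If the sponsor expects a material share of other causes, the sample size should be reconsidered with that share stated.

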### Assessment points

2.6

The main assessment and recording of the infants’ indicators will occur at the following time points (Table 1).

**Table 1 T1:** Neonatal assessment chart.

Measure	Assessment point							
	Allocation within 1 h after birth	4–10 h after PS	24 h	3 days	7 days	14 days	28 days	36 weeks CA/discharge
LUS	×	×	×	×	×	×	×	×
Clinical index								
Silverman Anderson score	×	×	×	×	×	×	×	×
Respiratory support mode	×	×	×	×	×	×	×	×
Ventilator parameters	×	×	×	×	×	×	×	×
Medication use of PS	×		×					
Outcomes assessment								
NIV (hours)								×
IMV (hours)								×
Supplemental oxygen (days)								×
PS (%)								×
Early PS (%)								×
Birth to the application of 1st PS (min)								×
LOS								×
Costs associated with hospital care								×
Complications								
hsPDA (%)								×
BPD (%)								×
IVH (%)								×
NEC stage I or II (%)								×
ROP (%)								×

NIV, non-invasive ventilation; IMV, invasive mechanical ventilation; Early PS, pulmonary surfactant administered within 3 h after birth; LOS, length of stay; hsPDA, hemodynamically significant patent ductus arteriosus; IVH, intraventricular hemorrhages; BPD, bronchopulmonary dysplasia; NEC, necrotizing enterocolitis; ROP, retinopathy of prematurity.

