### Planned intervention

2.7

All study participants will receive initial resuscitation in the delivery room or operating room following the latest European Resuscitation Council Guidelines for newborns (16), which dictate whether non-invasive or invasive ventilation should be administered. Subsequently, they will be transported to the NICU using a transport incubator. Throughout ventilation and transportation, a T-piece resuscitator will be utilized to provide either non-invasive or invasive respiratory support (Initial parameters: PEEP = 6 cmH2O, PIP = 15–20 cmH2O, FiO_2_≤0.4) in order to maintain the patient's target oxygen saturation. If the target oxygen saturation is not achieved, PEEP and FiO_2_ can be upregulated, but in order to avoid pneumothorax, PEEP should be controlled at ≤8 cmH2O (2). Our NICU implements the “golden one-hour” management for premature infants (17, 18). Premature infants with successful recovery will be transferred to the NICU ward within 15 min and reach a relatively stable state shortly after birth. Upon admission to the ward, all preterm infants will be randomly assigned to either the ultrasound or control group.

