### Therapy

2.8

Lung ultrasound procedure: The lungs will be partitioned based on the six-region method in the pulmonary ultrasound guidelines. Each lung will be divided into three regions: anterior, lateral, and posterior lung area. To do this, the anterior axillary line and the posterior axillary line will be used as boundaries. Both lungs will be divided into a total of six regions (19). An ultrasound probe perpendicular to the intercostals will be used to scan each area from the top to bottom and score it. A score of 0–3 (as proposed by Bratet al.) will be assigned to each scan area based on the ultrasound detected pattern; in the case of different score patterns in the same area, the worst will be selected (Figure 2) (14).

RDS lung ultrasound diagnostic criteria: (1) Lung consolidation with air bronchograms: this is the most crucial ultrasound manifestation of RDS, characterized by: (i) The degree and extent of consolidation correlate with disease severity. Mild RDS may exhibit consolidation limited to the subpleural areas, appearing focal and small in scope, while severe RDS demonstrates expanded consolidation areas, extending into deeper lung fields; (ii) consolidation may be observed in different lung fields on bilateral lungs or restricted to certain intercostal spaces on one side; and (iii) air bronchograms present as dense, snowflake-like, or spot-like patterns, with the consolidation area showing heterogeneous hypoechoic areas that are easily distinguishable from surrounding lung tissue; (2) Abnormal pleural lines and disappearance of A-lines; (3) Non-consolidated areas show changes resembling interstitial syndrome; (4) Bilateral points: these may be present during the acute phase of mild RDS or the recovery phase of severe RDS; and (5) pleural effusion: infants may exhibit varying degrees of unilateral or bilateral pleural effusion (19).

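### Exclusion criterion 4 removes infants for events after randomisation (death by 72 h, surgical transfer, incomplete data), so the groups compared may not be the groups randomised

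*Protocol article*

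**What the plan says.** Criterion 4 in section 2.2.2 (Exclusion criteria) excludes "infants who die within 72 h after birth, are transferred to another hospital for surgery, or have incomplete data". Criterion 2 in the same list excludes "infants with known or confirmed congenital abnormalities, especially cardiopulmonary deformities during diagnosis or treatment". Criterion 3 names severe complications at birth and closes with the clause "or other diseases not caused by PS deficiency", which carries no time limit of its own.

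On timing, section 2.7 (Planned intervention) states: "Upon admission to the ward, all preterm infants will be randomly assigned to either the ultrasound or control group". It also states: "Premature infants with successful recovery will be transferred to the NICU ward within 15 min". Section 2.3 (Randomization) likewise places allocation after transfer to the ward. Section 2.7.1 has the ultrasound arm scanned within an hour of admission, so after allocation. Section 2.5 (Blinding) says that the ultrasound physicians and neonatologists know the group from the start.

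The primary outcome (section 2.9) is total hours of invasive and non-invasive ventilation in hospital. Section 2.12 plans for 96 h against 86 h, SD 12 h in each group, with 24 infants per group raised to 30.

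**The concern.** An eligibility rule should use only what is known before allocation. The three items of criterion 4 lie in the future when the infant is randomised, so in practice they are removals from the analysis written as exclusions. The trial strategy decides whether and when surfactant is given, and the Background itself credits early surfactant with lower mortality. Early death may therefore be a consequence of the arm, and criterion 4 deletes it. What counts as incomplete data is not defined, and the staff who scan and treat know the allocation. Criterion 2 and the last clause of criterion 3 leave room for further removals after allocation.

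Two things are at stake. Once removal depends on prognosis and on arm, a difference in ventilation hours can no longer be credited to the strategy. And deaths in the first three days, which anyone judging a surfactant strategy would want to see by arm, are not in the comparison at all.

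**Working it through.** **1. Order of events.** Birth; arrival on the ward within about 15 min; randomisation on admission; first scan in the ultrasound arm within 1 h of admission; then the items of criterion 4. Death by 72 h, surgical transfer and incomplete data can be established only after allocation. Nothing in section 2.13 (Statistical analysis) returns these infants to the comparison.

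**2. The protocol's own sample size.** Inputs from section 2.12: difference 96 − 86 = 10 h, SD 12 h, α = 0.05, power 80%, ratio 1:1. Sidedness is not stated.

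- Normal approximation, two-sided: n = 2 × (1.96 + 0.84)² × 12² / 10² = 22.6, so 23 per arm. One-sided would give 18.
- Exact t-test, two-sided: power is 78.9% with 23 per arm and 80.7% with 24, so 24 per arm, as stated.
- Inflation: 48 / 0.80 = 60, that is 30 per arm, as stated.

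The sample size is sound on its inputs. The point here is bias.

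**3. Power if everyone is kept.** With 30 per arm, 10 h and SD 12 h, the exact t-test has 88.8% power, against 80.7% with 24 per arm.

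**4. What one-sided loss can do.** The protocol gives no exclusion rates, so this is an illustration under assumptions. In 40,000 simulated trials, both arms have 30 infants drawn from Normal(96, 12), there is no true effect, the infants removed are those with the longest durations, and the rest are compared by t-test at 5%.

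| Removed, ultrasound arm | Removed, control arm | Spurious difference (h) | Type I error |
|---|---|---|---|
| 0 | 0 | 0.0 | 4.8% |
| 1 | 0 | 0.9 | 6.5% |
| 2 | 0 | 1.6 | 9.0% |
| 3 | 0 | 2.2 | 12.8% |
| 6 | 0 | 4.1 | 28.1% |
| 3 | 1 | 1.4 | 9.6% |
| 6 | 3 | 1.8 | 13.8% |

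Here the ultrasound arm gains a false advantage. If the control arm lost more, the sign would reverse. The illustration suits transfers and incomplete records of infants with long ventilation. It does not describe early deaths, whose observed hours are short.

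**The case against.** The best defence is that the listed complications in criterion 3 are qualified as present at birth and that section 2.3 randomises eligible patients, so most exclusions read as screening before allocation. For those named conditions that stands. It does not reach criterion 4, whose items cannot be screened for, nor the open-ended wording in criteria 2 and 3. Nor is this a detail left to an analysis plan: the protocol sets the rule, and a later plan that kept these infants would contradict it.

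Several stronger readings are tempting and are not supported:

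- **That the bias could equal the whole planned effect.** Losing 3 of 30 infants shifts a mean by 10 h only if they were ventilated about 100 h longer than the rest (3 × 100 / 30 = 10). That is 100 / 12 = 8.3 of the protocol's SDs.
- **That an arm with more early deaths must look better.** An infant dead by 72 h has at most 72 observed hours, below both planned means (86 h and 96 h). Compared with counting observed hours, excluding such infants raises that arm's mean. The arm is flattered only if death is ranked as a bad outcome.
- **That infants are excluded on what the scan shows.** Section 2.2.2 mentions no scan, and section 2.1 and Table 1 have every enrolled infant scanned in the first hour. Unequal detection between arms is not established.
- **That the plan expects to lose 12 infants.** The 20% inflation in section 2.12 covers a low effect size as well as dropout.
- **That severe NEC goes unrecorded.** Table 1 is labelled "NEC stage I or II", but section 2.9 lists NEC without a stage limit and section 2.10 stages it by modified Bell criteria.

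**Conclusion.** The concern holds for criterion 4, and for criteria 2 and 3 so far as their wording lets them be applied after allocation. The protocol fixes a rule that removes randomised infants for later events that may depend on the arm, in a trial whose treating staff are unblinded. It also takes early deaths out of the comparison. This should be changed before the data are analysed.

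The size and direction of the bias are unknown. The illustrative figures (about 2 h and 13% type I error when 3 of 30 are lost from one arm, about 4 h and 28% when 6 are lost) rest on normal durations with SD 12 h, no true effect, and loss of the longest-ventilated infants from one arm only. They show that modest unequal loss matters; they do not predict this trial. The 20% inflation helps power, but it cannot restore comparability.

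**What to change.** - Delete criterion 4 as an exclusion, and limit criteria 2 and 3 to facts known before the envelope is opened.
- Analyse every randomised infant in the assigned arm, and report early deaths, transfers and missing data by arm.
- State in advance how death enters the primary comparison, for example as the worst rank in the Mann-Whitney test already named in section 2.13.
- Obtain ventilation end dates for transferred infants from the receiving hospital, and handle missing durations by a stated method.
- Keep an analysis restricted to confirmed NRDS as a sensitivity analysis only.

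**Cost.** Beyond wording, the main cost is that a rank analysis replaces the difference in mean hours as the primary summary. The t-test calculation in section 2.12 then no longer matches the analysis exactly, and the power should be restated. The estimated effect may be smaller. On the protocol's own inputs, keeping all 60 infants calls for no extra recruitment.

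**Minor, in the same edit.** Section 2.2.2 lists pleural effusion among the severe complications that exclude, while the ultrasound criteria for RDS in section 2.8 include "pleural effusion: infants may exhibit varying degrees of unilateral or bilateral pleural effusion". The two passages must be reconciled; a clarification of severity or timing may be enough. The NEC label in Table 1 should be brought into line with sections 2.9 and 2.10.
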